**Fig. 1 Fig1:**
[figure not shown]
Study flow chart according to the Consolidated Standards of Reporting Trials

For patients randomized to the NIV arm, NIV is initialized using a regular oral/nasal mask. Pressure support will be initiated with 18/4 mbar for adaptation and then increased to achieve effective respiratory support while trying not to lose tolerance.

With both devices, oxygen should be supplemented to reach an O_2_ saturation range of 88–92%. Patients should use respiratory support as long as possible, both day and night. The study intervention can be initiated at the emergency room or in intermediate or intensive care or a specialized respiratory medicine ward as mentioned above. The use of either device does not require alteration to usual care pathways (including use of any medication), and these will continue for both trial arms.

Statistical monitoring based on data in the database will take place at regular intervals and include the verification that reasons for switching devices are documented in a timely manner and follow the protocol specification. It will also be used to ensure that investigators provide the duration of device use as a measure of patient compliance. Departures at the site level from protocol specifications will lead to corrective measures.

Patients are covered by insurance while in the trial and after the trial; treatment is at the physician’s discretion but may include the continued use of the prescribed device.

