In case of premature termination of therapy, it is necessary to document the date (as exactly as possible), the reason of termination and the current condition of the patient. Therefore, the eCRF “End of study (ES)” has to be completed for each patient. Data entry to this eCRF page will trigger an automatic report to the responsible trial team members at the ZKS Leipzig.

After a patient has been enrolled, it is the investigator's responsibility to avoid protocol violations in order to obtain unbiased data for the trial. Those protocol violations deemed to be major are defined by the risk analysis performed before and during trial implementation and will be further detailed in separate documents belonging to the risk assessment/monitoring plan. This list can be augmented in the course of the trial. Major protocol violations will be reported to the coordination centre Leipzig, which will inform the co-ordinating investigator. All protocol violations will be documented and discussed with the responsible biometrician before closing the data base and carrying out the statistical analysis. The investigator must ensure that the recorded data are documented as per protocol. Minor variations are inevitable in clinical routine but must be documented together with a justification.

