### Sample size and statistical analysis

We followed statistical guidelines, recommending that clinical and statistical considerations be taken into account along with historical data when choosing a margin of non-inferiority [30]. Moreover, we note that the European Medicals Agency (EMA) and the Food and Drug Administration (FDA) often find proposed margins too lax and chose a stricter margin than the 15 and 10 percentage points used in two RCTs with non-inferiority designs for ventilation failure [5, 18, 24]. The point estimate from historical data for absolute risk reduction in intubation proportions due to NIV was found to be 20.7 and 11.9 with lower 95% confidence limits of 2.0 and 1.6 percentage points, respectively [5, 7, 8]. Taken all this into consideration, we chose Δ = 8 percentage points for our non-inferiority margin. The cited trials by Plant et al. and Carrera et al. found need for intubation in 13.5% and 15.1% of the NIV groups. We use this as a proxy for our endpoint and assuming that treatment failure is 15% in both arms, implying that 680 patients need to be analysed to have 80% power for having the upper end of the 95% CI within the margin of non-inferiority (continuity corrected *Z*-test with pooled variance) [31]. Taking into account a small drop-out rate of about 5%, we intend to recruit 720 patients in total.

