The full analysis set (FAS, based on the intention-to-treat (ITT) strategy) is defined to comprise all randomized patients with AECOPD and started on ventilatory support. If, for example, pneumonia is detected within 48 h (nosocomial), such patients will not be included in the final analysis, since the initial AECOPD diagnosis is found to be erroneous. Patients who test positive for SARS-CoV-2 within 48 h will not be included in the full analysis set. For the confirmatory analysis, linear regression with the stratification variables and the arm as covariates will be used and where the dependent variable will be coded as 0, 1. A 95% two-sided Wald confidence interval for the arm term can then be interpreted in terms of absolute risk and the null hypothesis is rejected if it does not cross the non-inferiority margin. As a sensitivity analysis, a two-sided 95%-Wilson confidence interval for the difference in proportions will be calculated. Only few missing data regarding all relevant endpoints are expected given the rather short period of observation. Nevertheless, conservative imputations will be performed independent of treatment arm. Further sensitivity analyses are planned to adjust for covariates, possibly imbalanced baseline characteristics between groups and/or protocol deviations in multivariable regression models, e.g. for (components of) the primary endpoint and/or in subgroups, which arose from stratification criteria. Furthermore, the odds ratios from logistic regression will be computed to have a relative risk measure in addition to the absolute one, as recommended by statistical guidelines.

Absolute risk differences of major secondary endpoints will be analysed in the same way as the primary endpoint. Kaplan-Meier curves/results of logrank tests will be presented for 28 and 90 days mortality. We expect the time to death to be (nearly) always available. Ventilator-free hours (until 72 h assessment) and SRI and SGRQ at 28 days will be analysed by a linear regression model including randomization arm as factor and stratification criteria as covariates. SRI and SGRQ cannot be determined at baseline due to the patients’ state.

Neither imputation of missing values nor adjustments for multiple testing are planned for secondary/safety endpoints. No interim analysis is planned.

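### A planned sensitivity analysis adjusts the arm effect for protocol deviations, which can arise after randomisation; that adjusted estimate is open to bias in either direction and is not a valid robustness check of non-inferiority

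*Protocol article*

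**What the plan says.** The confirmatory analysis is clearly fixed (Sample size and statistical analysis). In the full analysis set, "linear regression with the stratification variables and the arm as covariates will be used" with a 0/1 outcome, and "A 95% two-sided Wald confidence interval for the arm term" is compared with the margin of 8 percentage points.

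The same section then says: "Further sensitivity analyses are planned to adjust for covariates, possibly imbalanced baseline characteristics between groups and/or protocol deviations in multivariable regression models". It gives the primary endpoint or its components, and subgroups, as examples. The words at issue are "and/or protocol deviations in multivariable regression models". Deviations therefore stand beside baseline characteristics as things to adjust for in a regression.

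Other sections bear on what a deviation is:

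- **Randomization, recruitment and data collection.** Avoiding violations is described as the investigator's task once a patient is enrolled. "All protocol violations will be documented and discussed with the responsible biometrician" before the database is closed.
- **Interventions.** Statistical monitoring includes "verification that reasons for switching devices are documented in a timely manner and follow the protocol specification".
- **Study endpoints.** A switch to another non-invasive method within 72 h is a component of treatment failure, and the section limits when a switch should be considered.

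**The concern.** A variable that arises after randomisation is not protected by it. Deviations could plausibly differ by arm: the trial is open label, centres know NIV better than NHF (Discussion), and NIV is often poorly tolerated (Background). They may also share causes with failure, such as severity. Conditioning on them can remove part of the arm effect, where the deviation lies on the path to failure. It can also create a spurious arm effect, where deviation and failure share an unmeasured cause. An out-of-criteria switch is the extreme case, because part of the outcome then sits among the covariates.

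The adjusted arm term then estimates neither the intention-to-treat effect nor a defined per-protocol effect. In a non-inferiority trial readers look closely at how deviations were handled, because deviations can make arms look alike. A deviation-adjusted estimate could reassure or alarm them without good reason.

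**Working it through.** **1. The plan's own figures.** Inputs from the article: 15% failure in both arms, margin 8 points, two-sided 95% interval, 80% power, continuity correction, about 5% drop-out.

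- Without correction: n = 2 × 0.15 × 0.85 × (1.960 + 0.842)² / 0.08² = 312.7 per arm.
- With the Fleiss continuity correction: 312.7/4 × [1 + √(1 + 4/(312.7 × 0.08))]² = 337.3, so 338 per arm and 676 in total. The article has 680.
- Continuity-corrected power at 340 per arm is 80.3%. For drop-out, 680/0.95 = 716, close to 720.

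The sample size reproduces, and the point below does not touch it.

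**2. What adding a deviation term does.** Let D be a 0/1 deviation. In least squares with arm only, versus arm plus D:

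adjusted arm effect = unadjusted arm effect − γ × δ

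Here δ is the deviation rate on NHF minus that on NIV. γ is the within-arm slope of failure on deviation, that is, the sum over arms of cov(D, failure) divided by the sum over arms of var(D). If δ = 0 or γ = 0, nothing moves. Otherwise the sign follows δ and γ.

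**3. Sizes.** All deviation inputs are assumptions. The true difference is +8 points, so NHF is exactly at the margin and non-inferiority should be declared in about 2.5% of trials. In B to D, an unmeasured severity factor U has 50% prevalence, so var(U) = 0.25. Stratification covariates are left out for simplicity.

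- **A. Equal deviation rates.** δ = 0, so the shift is 0.
- **B. U raises failure by 20 points and deviation by 20 points; deviation rates 30% NHF, 15% NIV.** Mean covariance 0.2 × 0.2 × 0.25 = 0.010; mean variance (0.2100 + 0.1275)/2 = 0.16875; γ = 0.0593. Shift 0.0593 × 0.15 = 0.9 points, so the estimate is 7.1.
- **C. U raises failure by 20 points and deviation by 40; rates 45% and 25%.** γ = 0.020/0.2175 = 0.0920. Shift 0.0920 × 0.20 = 1.8 points, so the estimate is 6.2.
- **D. Rates as in B, U raises failure by 10 points, and the deviation itself raises failure by 20.** γ = 0.20 + 0.005/0.16875 = 0.2296. Shift 0.2296 × 0.15 = 3.4 points, so the estimate is 4.6.
- **E. The deviation is an out-of-criteria switch, in 40% of NHF failures and 20% of NIV failures.** By the endpoint definition no non-failing patient can have one. Rates are 0.40 × 0.23 = 0.092 and 0.20 × 0.15 = 0.030, so δ = 0.062. γ = (0.092 × 0.77 + 0.030 × 0.85)/(0.092 × 0.908 + 0.030 × 0.970) = 0.0963/0.1126 = 0.855. Shift 5.3 points, so the estimate is 2.7.

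Simulated rates of declaring non-inferiority (340 per arm, estimate + 1.96 SE below 0.08):

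| Scenario, true +8 | Not adjusted | Adjusted for D |
|---|---|---|
| A | 2.4% | 2.4% |
| B | 2.6% | 4.6% |
| B with arms' deviation rates swapped | 2.3% | 1.3% |
| C | 2.2% | 8.4% |
| D | 2.1% | 21% |
| E | about 2.5% | 53% |

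**4. The other direction.** With truly equal arms and scenario B's rates swapped (more NIV deviations), the adjusted estimate is +0.9 points and the chance of showing non-inferiority falls from 84% to 72%. In a stronger set-up the log-odds of failure and of deviation each rise by 1 per SD of severity, with deviations 20% NIV and 5% NHF. The estimate is then about +1.7 and the chance falls from about 83% to 62%.

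**5. Does excluding deviators cure it?** In that stronger set-up, excluding deviators gives about +1.6. With a true +8 and deviations 20% NHF and 5% NIV, adjustment gives about 5.8 and exclusion about 5.7. So exclusion is practically as biased. In scenario E, a set that does not count endpoint events as deviations loses nobody and keeps the 8 points.

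**The case against.** The best defence is that the article commits to little. The sentence is condensed and permissive, and names no deviation variable or coding. Major violations are left to separate risk and monitoring documents, and a full protocol and SAP are to be published. This stands in part. Which deviations would enter cannot be known from the article, and the lack of a described per-protocol set is no fault in a journal summary. But the sentence does name a method, regression adjustment for deviations, and that method is the point here.

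Three stronger readings are tempting, and the document supports none of them:

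- **That the analysis is biased as such.** Bias needs deviation rates that differ by arm and a link between deviation and failure. The article gives neither. With rates of 10% and 5% in the logistic set-up, a true +8 is estimated at 7.2; with equal rates it does not move. Deviations fixed before randomisation, such as eligibility violations, do not cause this problem.
- **That the non-inferiority conclusion could be made or unmade by it.** The article gives the deviation analysis no role in the decision, which rests on the full analysis set and the arm-plus-stratification model.
- **That a per-protocol set would be a clean replacement.** Step 5 of the working shows it need not be.

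**Conclusion.** The point holds as one about a stated sensitivity analysis. Adjusting for post-randomisation deviations leaves the arm term open to bias in either direction, so agreement or disagreement with the main result says little about robustness. In the illustrations a true difference at the 8-point margin is estimated anywhere from unchanged to 2.7 points when NHF has more deviations, and at 8.9 in the mirrored scenario B. The largest shift arises when the deviation is itself an endpoint event. All sizes rest on assumed deviation rates and associations, and on a linear model without stratification terms. That the adjustment can mislead does not depend on those particular values; how far, and which way, does.

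**What to change.** In the analysis plan, limit covariate adjustment in the sensitivity models to variables fixed before randomisation, and delete post-randomisation protocol deviations from the covariates.

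If a deviation analysis is wanted, make it supplementary and state its estimand. Two options:

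- **A per-protocol set** analysed with the confirmatory model. The deviation list is fixed before database lock without sight of outcomes, and endpoint events are not counted as deviations.
- **Inverse-probability weighting**, with its assumptions written down.

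State in the plan that simple per-protocol exclusion also conditions on post-randomisation events and can be equally biased. Its result is read beside the full-analysis-set result and does not replace it.

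The cost is a change of wording and, if the supplementary analysis is kept, one further analysis and a deviation list. The review of violations before database closure is already planned. The per-protocol set would be smaller and its interval wider. The confirmatory analysis and sample size need no change.

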### Study endpoints

The primary endpoint is the proportion of patients with treatment failure within 72 h. Treatment failure is defined by (a) switch to another method of non-invasive ventilation or (b) intubation or (c) death.

It is highly recommended that intubation only be initiated if pH < 7.15 and at least one of the following criteria is met: (i) Glasgow Coma Scale (GCS) < 10, (ii) O_2_ saturation < 85% or PaCO_2_ < 45 mmHg despite FiO_2_ > 0.5 and (iii) respiratory rate > 40 cycles/min.

Switching to another method of non-invasive ventilation should only be considered in the following situation:
One of the following criteria is met within 1 h: decrease in pH by at least 0.06, increase in pCO_2_ by at least 10 mmHg, unacceptable decrease in GCS, increase in respiratory rate by at least 20%, insufficient complianceOne of the following criteria is met after 2 h: unacceptable decrease in pH or pCO_2_, clinically unstable compared to last status (beginning at 4 h), insufficient compliance

The most important secondary endpoints are as follows: (a) proportion of patients that fulfil single components of the primary endpoint (i.e. intubation, switch of device or death within 72 h), (b) proportion of patients intubated within 7 days after hospitalization/randomization, (c) overall survival at 28 and 90 days, (d) (invasive) ventilator-free days up to day 28, (e) (invasive) ventilator-free hours until 72 h or until reaching the primary endpoint (whichever comes first), (f) ICU and hospital lengths of stay, (g) proportion of patients requiring sedation and (h) quality of life at day 28 according to St George’s Respiratory Questionnaire (SGRQ) and the Severe Respiratory Insufficiency (SRI) questionnaire, both of which are validated and standard instruments used in patients with obstructive airway diseases [27–29]. Safety issues of interest are device related intolerance/complications and severe diseases acquired under treatment. Compliance and acceptance of devices will also be investigated.

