### Randomization, recruitment and data collection

Randomization will be performed centrally, via a secure web-based tool. The allocation to the intervention arm (randomization ratio 1:1) uses a minimization procedure with a stochastic component that takes into account trial centre, pH ≤/> 7.3 and BMI ≤/> 30 kg/m^2^. The randomization result forwarded automatically via email to the investigator and the Clinical Trial Centre Leipzig.

Adequate recruitment will be encouraged through regular Newsletters including current recruitment status, regular consultations with trial sites by the monitor/coordinating investigator and trial meetings.

The schedule of study visits and list of parameters collected can be found in Table 1. Within the first 24 h, data are collected at 1, 2, 4, 6, 12 and 24 h after which collection takes place at 36, 48 and 72 h. There is a discharge visit and one at day 7 as well as telephone visits on days 28 and 90.

**Table 1 Tab1:** Schedule for study interventions according to Recommendations for Interventional Trials (SPIRIT) indications

Examination/assessment		Treatment											Follow-up		
	Screening	Visit 0	Visit 1						Visit 2		Visit 3		Visit 4	Visit 5^**a**^	Visit 6^**a**^
Timepoint		0 h	1 h ± 30 min	2 h ± 30 min	4 h ± 30 min	6 h ± 30 min	12 h ± 60 min	24 h ± 60 min	36 h ± 90 min	48 h ± 120 min	72 h ± 180 min	discharge	day 7^**b**^ ± 1 day	day 28	day 90
Informed consent	X^c^											X^d^			
Inclusion criteria/exclusion criteria	X														
Randomization		X													
Patient characteristics (anamnesis, comorbidity)	X														
Medication	X							X^e^		X^e^	X^e^	X			
Clinical parameters (heart rate, respiratory rate, blood pressure, Borg’s scale)	X		X	X	X	X	X	X	X	X	X	X	X		
Adverse events/side-effects			X	X	X	X	X	X	X	X	X	X	X	X	X
Glasgow coma scale (GCS)	X		X	X	X	X	X	X	X	X	X	X			
Blood gas analysis (BGA): pO_2_, pCO_2_, pH, SpO_2_, FIO_2_	X		X	X	X	X	X	X	X	X	X	X	X		
Therapy according to allocated device: device parameters		X	X^6^	X	X	X	X	X	X	X	X	X	X^g^	X^f^	X^f^
Therapy: oxygen supplement		X	X	X	X	X	X	X	X	X	X	X	X^f^	X^f^	X^f^
infection parameters and biomarkers (optional)	X							X^e^			X^e^				

^a^Visits 5 and 6 are conducted by telephone

^b^Assessment of intubation; not applicable, if patient is already discharged since no intubation can be stated in this care

^c^Standard (long) version of informed consent OR concise (short) version of informed consent

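### The stated survival comparison for 28- and 90-day mortality does not use the minimisation factors and gives no hazard ratio; the test is valid, and the remedy is a small, free improvement

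*Protocol article*

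**What the plan says.** All places are in the Methods of the protocol article.

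- **Allocation** (Randomization, recruitment and data collection): 1:1 by a minimisation procedure that "takes into account trial centre, pH ≤/> 7.3 and BMI ≤/> 30 kg/m^2".
- **Endpoint** (Study endpoints): item (c) in the list of the most important secondary endpoints is "overall survival at 28 and 90 days".
- **Time-to-event analysis** (Sample size and statistical analysis): "Kaplan-Meier curves/results of logrank tests will be presented for 28 and 90 days mortality". The sentence mentions no stratification, hazard ratio or interval.
- **The sentence just before it**: "Absolute risk differences of major secondary endpoints will be analysed in the same way as the primary endpoint". For the primary endpoint, "linear regression with the stratification variables and the arm as covariates will be used", and "A 95% two-sided Wald confidence interval for the arm term can then be interpreted in terms of absolute risk".
- **Other secondary endpoints** (same paragraph): ventilator-free hours, SRI and SGRQ get a linear model with arm as factor and the stratification criteria as covariates.

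**The concern.** The article carries the minimisation factors into the analysis of the primary endpoint, ventilator-free hours and quality of life. For the survival comparison it names only a logrank test. If pH and BMI group predict death, minimisation makes the arms more alike on these factors than chance would. A test that ignores them then uses a variance slightly too large for the design, which makes it conservative and costs some power.

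A logrank p-value also does not say how large an excess of deaths the data leave open. That question matters here. The Discussion says the comparator, NIV, has been shown to reduce mortality, and the primary composite counts device switches alongside intubation and death, so it may say little about deaths alone. An estimate with an interval is needed, and the sentence on risk differences that would supply one does not name mortality.

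**Working it through.** **1. The plan's own figure.** The article gives no event count or power for mortality, so only the number of patients can be checked. Inputs: 15% failure in both arms, margin 0.08, two-sided 95% CI, 80% power, continuity correction.

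- Uncorrected: n0 = 2 × 0.15 × 0.85 × (1.960 + 0.842)² / 0.08² = 312.7 per arm.
- Corrected: n = (n0/4) × [1 + √(1 + 4/(n0 × 0.08))]² = 337.3, so 338 per arm, 676 in total. The article says 680.
- Drop-out: 680/0.95 = 716. The article says 720.

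Both agree closely, and 680 is used below.

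**2. What omitting the factors costs.** Two simulations compared the unstratified and stratified logrank test (statistic summed over strata, rejection at |Z| > 1.96). Both used exponential survival censored at 90 days, half the patients in the low-pH group, arms balanced on the factors and a treatment hazard ratio (HR) of 1.6. Mortality and factor strengths are assumptions; the article gives no planned mortality rate.

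*A. Stratified by pH only.* 18.3% mortality (the background figure of 183 deaths per 1000 as a stand-in), 4,000 runs per setting.

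| HR of the pH factor | Power unstratified | Power stratified | Gain (points) |
|---|---|---|---|
| 1.5 | 82.1% | 82.5% | 0.4 |
| 2.5 | 81.6% | 82.7% | 1.1 |
| 4 | 80.1% | 82.6% | 2.5 |

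*B. Stratified by pH × BMI, then also by 35 centres.* About 15% baseline mortality, a quarter of patients in the high-BMI group, 1,500 runs per setting.

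| HR for pH, HR for BMI, SD of centre effect | Unstratified | pH × BMI | pH × BMI × centre |
|---|---|---|---|
| none (1, 1, 0) | 77.2% | 77.1% | 74.1% |
| weak (1.5, 1.2, 0.2) | 77.1% | 77.1% | 74.7% |
| moderate (2, 1.5, 0.3) | 76.8% | 77.5% | 74.4% |
| strong (3, 2, 0.5) | 77.9% | 80.2% | 78.5% |

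Where the factors matter, stratifying by pH and BMI gains 0 to 2.5 points. Adding centre mostly loses 2 to 3 points: 4 × 35 = 140 cells hold about 680/140 = 4.9 patients each.

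**3. Type I error of the unstratified test.** It was about 4.4% in A for the two stronger settings and 4.8% in B with moderate factors. The Monte Carlo standard error at 5% is √(0.05 × 0.95/4000) = 0.34 points in A and √(0.05 × 0.95/1500) = 0.56 points in B. This fits a valid, slightly conservative test; no inflation appears.

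**4. Why an interval is needed.** With d deaths, logrank power is Φ(ln(HR) × √d/2 − 1.96). With equal observed mortality p, the half-width of the 95% CI for the risk difference is 1.96 × √(2p(1−p)/340), and that for the HR runs from 1/k to k with k = exp(1.96 × 2/√d).

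| Assumed mortality | Deaths in 680 | Power, HR 1.5 | Risk-difference half-width (points) | k |
|---|---|---|---|---|
| 5% | 34 | 22% | 3.3 | 1.96 |
| 10% | 68 | 39% | 4.5 | 1.61 |
| 18.3% | 124 | 62% | 5.8 | 1.42 |
| 25% | 170 | 75% | 6.5 | 1.35 |

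These limits come from the number of deaths. Stratification hardly moves them.

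**The case against.** The strongest reply is that mortality already has an adjusted effect size. Overall survival is among the most important secondary endpoints, and the sentence before the logrank line gives major secondary endpoints a risk difference analysed like the primary endpoint, with the stratification variables and a 95% CI. On that reading the curves and the logrank test are additions. This largely stands and is the more natural reading. It is not certain: the word major is not defined, the list also holds endpoints that are not risks (lengths of stay, quality of life), and mortality has its own sentence.

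Second, the article does not call the test unstratified, and a condensed article may leave stratification and a Cox model to the full protocol or SAP, neither of which is shown. This also has force. What can be said is that the article states the adjustment for other endpoints in this paragraph and not for survival.

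Third, the gain is tiny, and its upper end needs a pH factor with HR 4, which nothing in the article supports. That is correct.

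A reader might infer more: that no effect size is planned for deaths, or that a non-significant logrank result will be taken as no excess deaths. The risk-difference sentence speaks against the first. The second appears nowhere in the article, and the 8-point margin is set for the primary endpoint only.

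**Conclusion.** The point holds as a minor one. As written, the time-to-event comparison of mortality leaves out the factors used in allocation and has no hazard ratio, unlike the adjusted analyses beside it. The test is valid and errs on the conservative side. The loss is about 0 to 2.5 points of power, resting on assumed mortality of about 15 to 18%, a treatment HR of 1.6 and assumed factor strengths; with weak factors it is close to nil.

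The low power for deaths (39% or 62% for HR 1.5 at 10% or 18.3% mortality) is not caused by the missing stratification and should not be argued that way. It is the reason to make the interval, rather than the p-value, the basis for judging excess deaths. The plan probably provides that interval but does not say so outright.

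**What to change.** In the SAP, and in the article's wording if it is revised:

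1. Stratify the logrank test by the pH and BMI minimisation groups. Leave centre out as too sparse.
2. Report the hazard ratio with 95% CI from a Cox model stratified or adjusted for the same two factors.
3. Confirm that the adjusted absolute risk differences with 95% CI cover 28- and 90-day mortality, and that they are the basis for judging excess deaths.

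The cost is a few lines of wording and code. pH and BMI group are already recorded for allocation, so no extra data are needed. Because the trial is open label and the analysts are not blinded, the wording should be settled before mortality is compared between arms. If the SAP already says this, nothing needs to change.
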